## **8. Study significance:**

Patients accessing public hospital services are rarely provided with engaging material to complement clinical care. Especially during the current COVID crisis, patients are isolated and lack engagement from their health providers.

The intervention assessed in this study, if validated, offers a simple, cost effective way to improve patient health and health literacy. Improved patient health literacy has been linked to better health outcomes in populations of patients with cardiovascular disease, and the potential for better medication adherence could see a direct translation from this study into better health outcomes.

Making use of time that is often wasted to improve patient experience and health is of high interest to health system administrators in both the private and public sectors.

## **9. Safety**

### **9.1 Data and Safety Monitoring Board (DSMB)**

Watching videos is safe and does not cause harm. A DSMB will not be required.

### **9.2 Adverse event definitions and reporting**

There are no anticipated adverse effects from the study intervention.

## **10. Ethics and Dissemination**

### **10.1 Research and ethics approval**

We will seek ethical approval from HREC Westmead Hospital.

### **10.2 Protocol Amendments**

Protocol modifications that could impact the conducting of the study (ie changes to the objectives, study design, subject population, study procedures) must be approved by the ethics committee, and regulatory authorities where required. It is expected that investigators take immediate action that may be required for subject safety, even if this is not in accordance with the protocol. Regulatory authorities and ethics committees should be notified of this within 72 hours.

### **10.3 Consent**

The study consenting documents are displayed in appendix 1. Potential participants will only be included in the study after reading and acknowledging the participant information form. This form outlines the pertinent details of the study to potential participants, including:

- Randomisation between intervention and control (1:1)
- Storage of data and data security/de-identification
- Access to patient data relevant to the study
- Right to receive treatment regardless of participation
- Right to withdraw from the study
- Consent to follow up phone contact from study coordinators at 90 days

Participants will be provided the study participant information form and contact details of relevant HREC staff and study investigators.

Investigators have developed the study information form and consent process such that pertinent study details can be communicated to participants in a way that respects their time whilst recognizing their right to understand the research they are agreeing to participate in and provide informed consent.

Study staff will also explain the details of the study and be available to provide additional information about the study to participants who request. All participants are free to withdraw from the study at any time. If withdrawal occurs, relevant study staff will not collect additional data, although data already collected will be retained to ensure the results of the research project can be measured properly and to comply with law. Data collected by the sponsor up to the time of withdrawal will form part of the research project results. If a patient doesn't want this to occur, they must tell the research team prior to joining the research project.

#### **10.4 Confidentiality**

All personal information in the central database will be de-identified. Participant information sheets and survey responses will be stored in a locked office in the Westmead Applied Research Centre only accessible by card. Data entered via study tablets will be stored in the secure RedCap server. The information will be re-identifiable for the research assistant that will be making 90 day follow up calls to participants.

#### **10.5 Post trial care**

All participants will be sent links to the videos to view in their own time after the 90 day follow up period.

#### **10.6 Declaration of Interests**

There are no competing interests from anyone in the study group.

5/6/2020

## eAppendix 2: Statistical analysis plan

### 1. Synopsis

Atrial fibrillation (AF) is the most common cardiac arrhythmia, with prevalence expected to double by 2050. Management of AF is complex, requiring patient adherence to potentially 3 classes of medication (rate/rhythm control, anticoagulation) and lifestyle modification. Patient education is a key component of holistic AF management, however there is limited availability of evidence-based education that is relevant to patients in Australian contexts. Clinician-created education may provide a solution to bridge this gap but there are few examples of randomised studies assessing its efficacy in improving patient knowledge, adherence, or satisfaction with clinical care.

This study aims to investigate in a randomised clinical trial (RCT), among 200 patients in inpatient and outpatient hospital settings with AF, the impact of continued exposure to a series of clinician-created educational videos on patient knowledge of AF at 90 days follow up compared to usual care. Key secondary outcomes will include satisfaction with clinical care, motivation to maintain medication adherence, and medication adherence.

### 1.1 Primary objective

To examine, in a randomised controlled trial of 200 hospital inpatients and outpatients with AF, the impact of continued exposure to clinician-created educational videos on AF knowledge at 90 day follow up.

**1.2 Secondary objectives**

To investigate whether, when compared to usual care, patients who are exposed to clinician-created videos are:

- More satisfied with their clinical care
  - Highly satisfied -  $\geq 6/7$  on Likert scale, not highly satisfied  $\leq 5/7$
- More motivated to adhere to AF medications at 2 and 90 days
  - Highly motivated -  $\geq 6/7$  on Likert scale, not highly motivated  $\leq 5/7$
- More adherent to medications at 90 days (see appendix 1: medication adherence questionnaire)

Non-adherence will be defined as

4. Response to question 1 of “Most of the time (75%) or less OR
5. Response to question 2 of “once per week” or more OR
6. Response to question 3 of “once per week” or more OR

**1.3 Trial design**

Randomised clinical trial with randomisation to intervention or control with ratio 1:1 respectively (n=200, intervention = 100, control = 100). Intervention participants will receive educational videos on top of usual care and control participants will receive usual care.

[figure not shown]

eFigure 1: Participant recruitment and follow up

#### 1.4 Interventions

Patients randomised to the intervention arm will, following completion of remote consent, receive access to a series of 4 educational videos describing AF, its pathophysiology, pharmacological management, and lifestyle modification.

#### 1.5 Subgroups

The interaction of treatment effect and age, gender, education, ethnicity, subtype of AF and category of presentation will be explored but the study is not powered for these subgroups.

#### 1.6 Power and sample size

A sample size of 200 participants (100 per arm) would, allowing for 15% attrition and assuming a standard deviation of 18 as described in other studies, have 90% power (2 sided, type 1 error of 5%) to detect an difference in 90-day AF knowledge of 8.95% between participants in the intervention and control arms of the study, which we consider a significant improvement in knowledge. Previous assessment of the JAFKQ has indicated participant scores 1-month post-test with no educational intervention are unchanged (60.4 [SD = 18.6] vs 62.3 [SD = 18.5];  $p = 0.551$ ). Analysis will follow intention to treat principles with all participants analysed in the arm they have been randomised to. P-values of  $< 0.05$  will be considered significant. Primary outcome analysis will use a two-tailed t-test to assess the difference between mean participant JAFKQ scores (max score = 100%). Analysis will also be performed utilizing an Analysis of Covariance (ANCOVA), with baseline JAFKQ scores and education level incorporated into the model as covariates.

For secondary analysis of satisfaction with clinical care, patient responses will be dichotomised into ‘highly satisfied’ ( $\geq 6/7$ ) vs ‘not highly satisfied’ ( $\leq 5/7$ ). For medication adherence, patients will be classified as “adherent” or “not adherent”. Proportions in intervention vs control arms will be compared using a chi-squared test. Relative risk will be calculated using a log binomial unadjusted and adjusted for total time in clinic (for outpatients) and number of medications. Allowing for 15% attrition and assuming 60% satisfaction/medium or greater adherence in the control groups, a sample size of 200 (100 per arm) would have 90% power to detect a relative risk difference in satisfaction and adherence between control and intervention groups of 1.37 (that is, an increase from 60.0% to 82.2%).

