### **7. Statistical considerations and Analysis:**

Analysis will follow intention to treat principles with all participants analysed in the arm they have been randomised to. P-values of  $< 0.05$  will be considered significant. Primary outcome analysis will use a two-tailed t-test to assess the difference between mean participant JAFKQ scores (max score = 100). Analysis will also be performed utilizing an Analysis of Covariance (ANCOVA), with baseline JAFKQ scores and education level incorporated into the model as covariates. A sample size of 200 participants (100 per arm) would, allowing for 15% attrition and assuming a standard deviation of 18 as described in other studies, have 90% power (2 sided, type 1 error of 5%) to detect an difference in 90-day AF knowledge of 8.95% between participants in the intervention and control arms of the study, which we consider a significant improvement in knowledge. Previous assessment of the JAFKQ has indicated participant scores 1 month post-test with no educational intervention are unchanged (60.4 [SD = 18.6] vs 62.3 [SD = 18.5];  $p = 0.551$ ).

For secondary analysis of satisfaction with clinical care, patient responses will be dichotomised into ‘satisfied’ ( $\geq 5/7$ ) vs ‘unsatisfied’ ( $\leq 3/7$ ). For medication adherence, patients will be classified as “adherent” or “not adherent as per page 11-12. Proportions in intervention vs control arms will be compared using a chi-squared test. Relative risk will be calculated using a log binomial unadjusted and adjusted for total time in clinic (for outpatients) and number of medications. Allowing for 15% attrition and assuming 60% satisfaction/medium or greater adherence in the control groups, a sample size of 200 (100 per arm) would have 90% power to detect a relative risk difference in satisfaction and adherence between control and intervention groups of 1.37 (that is, an increase from 60.0% to 82.2%).

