## 3. Analysis

### 3.1 Analysis Principles

#### General methodology

All statistical tests will be two-tailed, and a 5% significance level adopted throughout.

Analyses will be performed according to the principal of intention to treat and will include all randomised patients.

Summaries of continuous baseline variables will be presented as means and standard deviations together with medians and inter-quartile ranges. Categorical variables will be presented as frequencies and percentages. All

continuous data will be checked for normality

Methods for handling missing data are described in 3.2 – sensitivity analysis. If 80% of survey data is available, missing data will be imputed. Participants with less than 80% of outcome data available for a given survey will be removed from analysis.

Baseline values of the analysed parameter will be used as a covariate for analysis that support covariates, if these are not available see approach described below.

Balance in baseline risk factors will be considered between intervention and control groups, and if significant differences exist, additional regression analysis of outcome variables adjusting for this difference will be performed.

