#### **Primary outcome analysis:**

The primary outcome will be analysed utilising an analysis covariance (ANCOVA), with age, gender, education and subtype of AF incorporated as covariates. Where baseline data are available, this will also be incorporated into the model as a covariate. An unadjusted two-tailed t-test will also be performed. We will report p-values and 95% confidence intervals.

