##### 4.1.1 Primary and key secondary outcome Analysis

The primary outcome will be analysed utilising an analysis of covariance (ANCOVA) comparing scores between intervention and control groups and adjusting for age, gender, educational level and sub-type of AF.

The primary outcome will also be analysed utilising a two tailed t-test comparing the mean score on the JAFKQ between intervention and control participants. Primary and secondary analysis is described in etable 9.

eTable 9: Primary and key secondary outcome analysis

|                                                                    | Control
NC (%)   | Intervention
NT(%) | RR [95% CI]
(Control vs
CPR video)
[unadjusted] | RR [95% CI]
(Control vs
CPR video)
[adjusted] | p-value
[adjusted] |
|--------------------------------------------------------------------|----------------------------------------|------------------------------------------|--------------------------------------------------------------------|------------------------------------------------------------------|-------------------------------|
| Jessa Atrial Fibrillation Knowledge Questionnaire score (%) |                                        |                                          |                                                                    |                                                                  |                               |
| Mean score 2 days
post intervention                             | (n=xx)
Mean (SD)
Median
(IQR) | (n=xx)
Mean (SD)
Median (IQR)      |                                                                    | Mean
Difference
(95% CI)                                   | p-value                       |

| Mean score 90 days post intervention                | (n=xx)
Mean (SD)
Median
(IQR) | (n=xx)
Mean (SD)
Median (IQR) |  | Mean Difference
(95% CI) | p-value |
|-----------------------------------------------------|----------------------------------------|-------------------------------------|--|-----------------------------|---------|
| Satisfaction                                 |                                        |                                     |  |                             |         |

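### Protocol 7 and SAP 1.6 make an unadjusted t-test the primary analysis, SAP 3.1 and 4.1.1 put an ANCOVA first, and nothing says which governs

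*Combined protocol and SAP*

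**What the plan says.** The primary analysis is described in four places.

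- **Protocol section 7 and SAP 1.6.** Both put the t-test first; in the SAP's words, "Primary outcome analysis will use a two-tailed t-test to assess the difference between mean participant JAFKQ scores". Both then add a second analysis: "Analysis will also be performed utilizing an Analysis of Covariance (ANCOVA), with baseline JAFKQ scores and education level incorporated into the model as covariates".
- **SAP 3.1, primary outcome analysis.** "The primary outcome will be analysed utilising an analysis covariance (ANCOVA), with age, gender, education and subtype of AF incorporated as covariates". The next sentences bring in the baseline value where it is available, and add an unadjusted t-test.
- **SAP 4.1.1.** The primary outcome is analysed by "analysis of covariance (ANCOVA) comparing scores between intervention and control groups and adjusting for age, gender, educational level and sub-type of AF". The t-test again comes second. Baseline JAFKQ is not named.

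Three other parts of the SAP bear on the question. The general methodology in 3.1 has a rule that the baseline value of an outcome serves as a covariate in any analysis that can take one. The data collection schedule (eTable 1) has JAFKQ measured at baseline. eTable 9, the shell for the main results, has one p-value column, headed as adjusted.

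The general methodology also provides that, after a check of baseline balance, "if significant differences exist, additional regression analysis of outcome variables adjusting for this difference will be performed".

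**The concern.** A trial with one primary endpoint needs one primary test, fixed before the data are seen. Here the t-test is primary in two places and the ANCOVA leads in two others. The conflict lies inside the SAP (1.6 against 3.1 and 4.1.1), so the usual convention that a SAP overrides the protocol does not settle it.

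Two things are at stake. The first is error control. If the t-test and the ANCOVA fall on opposite sides of 0.05, the documents can be cited for either conclusion, and the nominal 5% holds only if the choice was fixed beforehand. The second is precision. Baseline JAFKQ is collected, and adjusting for it would narrow the confidence interval. That gain is lost if the t-test governs, or if the 4.1.1 model is fitted exactly as written there.

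**Working it through.** **Inputs from the documents (protocol 7 and SAP 1.6).** 100 per arm with 15% attrition, so 100 × 0.85 = 85 per arm evaluable; two-sided 5%; 90% power; "assuming a standard deviation of 18 as described in other studies"; target "difference in 90-day AF knowledge of 8.95% between participants in the intervention and control arms".

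**Input not in the documents.** The correlation r between baseline and 90-day JAFKQ. I take 0.3 to 0.7 as an assumption.

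**Step 1: reproduce the plan's figure.** The detectable difference for an unadjusted comparison is (1.960 + 1.282) × 18 × √(2/85) = 8.95 points. In the other direction, the power for 8.95 points is 0.900 by the normal approximation and 0.897 by the noncentral t. The plan's figure reproduces. It is a calculation for the t-test, with no term for baseline correlation.

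**Step 2: effect of baseline adjustment.** The residual SD becomes 18 × √(1 − r²). Any gain from the other covariates and the small loss of degrees of freedom are ignored. At 85 per arm:

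| Analysis | Residual SD | Detectable difference, 90% power | Power for 8.95 points |
|---|---|---|---|
| t-test | 18.00 | 8.95 | 90.0% |
| ANCOVA, r = 0.3 | 17.17 | 8.54 | 92.5% |
| ANCOVA, r = 0.5 | 15.59 | 7.75 | 96.3% |
| ANCOVA, r = 0.7 | 12.85 | 6.39 | 99.5% |

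**Step 3: type I error if either test may count.** With no true effect, the t statistic and the baseline-adjusted ANCOVA statistic are approximately bivariate normal with correlation √(1 − r²). The error rate is 1 − P(|Z₁| < 1.96 and |Z₂| < 1.96).

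| r | Correlation of the two statistics | Type I error |
|---|---|---|
| 0.3 | √0.91 = 0.954 | 6.4% |
| 0.5 | √0.75 = 0.866 | 7.3% |
| 0.7 | √0.51 = 0.714 | 8.3% |

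Each test on its own holds 5%. The excess arises only if the choice between them is left open.

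**Step 4: does the difference in covariate lists matter as much?** Very little, once baseline JAFKQ is in both models. A null simulation with 85 per arm and r of 0.5 to 0.7 gave about 5.5% to 5.7% when either of the two baseline-adjusted ANCOVAs (short list or long list) could count. Nearly all the inflation comes from the choice between the t-test and a baseline-adjusted ANCOVA.

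**The case against.** The strongest reply is that the SAP, read as a whole, does point to one analysis. The general rule in 3.1 calls for the baseline value as a covariate, the primary outcome paragraph of 3.1 repeats it, and JAFKQ is scheduled at baseline. On that reading 4.1.1 is a shortened restatement of the 3.1 model. eTable 9 leaves the unadjusted column blank for JAFKQ and reports an adjusted mean difference and p-value. The outlier is then SAP 1.6, a power section that largely repeats protocol 7.

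Most of this stands, and it shows which way to resolve the conflict. It does not resolve it, because 1.6 still states in plain terms that the t-test is primary and no sentence gives another section precedence.

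Four stronger readings are tempting but not supported.

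- **Baseline JAFKQ is discarded.** Section 3.1 says otherwise. The gain is unsecured rather than given up.
- **There are four rival analyses, with an error rate near 9%.** Simulation gives 8.4% to 9.3% if any of four models may count (r of 0.5 to 0.7, assumed). That treats 3.1 and 4.1.1 as separate models and supposes a rule that any significant result suffices, which the documents do not propose.
- **The trial is underpowered.** It is not under either test.
- **The baseline-imbalance rule would fire in most trials.** Counting 17 baseline variables in eTables 7 and 8 gives 1 − 0.95¹⁷ = 58%. Four of them (age, gender, education, AF subtype) are already in the ANCOVA, and 1 − 0.95¹³ = 49%. Both figures assume independence and that every row is a risk factor. The models so triggered are described as additional and replace nothing.

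**Conclusion.** The point holds. The primary test is stated in two incompatible ways, and the conflict sits within the SAP. The evidence favours a baseline-adjusted ANCOVA as the intended headline, but the text does not secure it.

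The cost is a type I error of about 6.4% to 8.3% instead of 5%, conditional on significance on either test being accepted and on r between 0.3 and 0.7. If the t-test governs, the trial also forgoes a fall in detectable difference from 8.95 points to between 8.54 and 6.39. Both ranges depend on a correlation that the documents do not give; at the low end the precision gain is modest.

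The stated 90% power needs no correction: it is right for the t-test and conservative for the baseline-adjusted ANCOVA. The text should be settled before any comparison by arm is run.

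**What to change.** State one primary analysis in the same words in protocol 7 and SAP 1.6, 3.1 and 4.1.1: ANCOVA of 90-day JAFKQ on arm, with baseline JAFKQ (by name), age, gender, education and AF subtype. Label the t-test supportive wherever it appears. Add a sentence that the primary conclusion rests on the ANCOVA estimate, its 95% confidence interval and its p-value alone. In the power text, note that the calculation is for the unadjusted comparison and so is conservative.

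As a minor point, label any model triggered by significant baseline differences (SAP 3.1, general methodology) as exploratory, or drop it.

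The cost is wording only, with no new data or participants. The small downside is that the headline estimate becomes a model-adjusted difference; the raw difference in means can still be shown beside it.

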## 2. Patient Population

The study population will be patients with confirmed AF on an electrocardiogram presenting to Westmead Hospital for clinical care. This includes both inpatients and outpatients.

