#### **Secondary outcome analysis:**

The significance of any difference between proportional secondary outcomes (satisfaction with clinical care, motivation to maintain adherence, actual medication adherence) will be analysed using a log binomial model adjusting for age (continuous), gender (male vs female), education (year 11 and above vs less than year 11), subtype of AF (categorical). A relative risk, 95% confidence interval and p-value will also be reported. Where baseline results are available, the corresponding baseline value results (e.g. discrete total score) will also be included as a covariate. Where this does not converge, a robust poisson will be fitted.

An unadjusted chi squared test will also be calculated with a corresponding relative risk, 95% confidence interval and p-value.

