#### 5.1.1 Satisfaction with clinic, motivation to maintain medication adherence and medication adherence – Analysis

Key secondary outcomes (satisfaction, motivation to maintain medication adherence and medication adherence) will be assessed utilising a log binomial adjusting for age, gender, educational level and sub-type of AF. This analysis is encompassed within table 9.

An unadjusted chi-squared test will also be performed comparing these two outcomes.

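### Two adjusted models with no covariate in common are prespecified for satisfaction and adherence, and one of them uses clinic time, which has no rule for inpatients and no stated timing

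*Combined protocol and SAP*

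**What the plan says.** Protocol section 7 and SAP 1.6 specify the relative risk for satisfaction and adherence in nearly the same words. SAP 1.6 reads: "Relative risk will be calculated using a log binomial unadjusted and adjusted for total time in clinic (for outpatients) and number of medications". In protocol section 7 it is likewise to be estimated unadjusted, and also "adjusted for total time in clinic (for outpatients) and number of medications".

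SAP 3.1 (secondary outcome analysis) specifies a different model for satisfaction, motivation and adherence: a "log binomial model adjusting for age (continuous), gender (male vs female), education" and AF subtype. Where a baseline result exists, "the corresponding baseline value results (e.g. discrete total score) will also be included as a covariate".

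SAP 5.1.1 says that the same three outcomes "will be assessed utilising a log binomial adjusting for age, gender, educational level and sub-type of AF". It does not mention the baseline value, and it refers to the SAP's table 9 for the results.

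On the population, SAP section 2 says: "This includes both inpatients and outpatients". SAP 3.1 requires intention-to-treat analyses that cover everyone randomised.

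**The concern.** The adjusted result for a key secondary outcome should come from one model fixed in advance. Here two are written down. No sentence ranks them or labels one a sensitivity analysis, and eTable 9 has room for only one adjusted relative risk. Its only p-value column is also headed as adjusted, so the reported p-value for satisfaction and adherence depends on a choice that could be made after the data are seen.

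The model with clinic time has two further weaknesses. The text ties that covariate to outpatients, but inpatients are in the trial and no rule says how they enter the model. Clinic time also appears to be completed after allocation. If the videos change the length of a visit, and visit length is related to satisfaction, conditioning on it can remove part of the effect or introduce bias.

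**Working it through.** **1. The covariate sets side by side**

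| Source | Covariates in the adjusted log-binomial model |
|---|---|
| Protocol 7 and SAP 1.6 | total time in clinic (outpatients), number of medications |
| SAP 3.1 | age, gender, education, AF subtype, baseline value where available |
| SAP 5.1.1 | age, gender, educational level, AF subtype |

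The first row has no term in common with the other two. The second and third differ only in the baseline value. The general methodology in SAP 3.1 supports including that term, since it calls for the baseline value as a covariate wherever the method allows one. Under the collection schedule (eTable 1), adherence and motivation have a baseline measurement and satisfaction does not. The fallback to robust Poisson in SAP 3.1 changes the fitting method, not the covariates.

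**2. Who has a clinic time**

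Inpatients are eligible (protocol 3.2, SAP 2). The covariate is restricted to outpatients, and no rule follows: a separate outpatient model, a term omitted for inpatients, or exclusion of inpatients. Outpatients may also attend by telehealth (protocol 3.3). Clinic time is never defined, so whether they have a value is open. The variable appears neither in the baseline data list in protocol section 5 nor in either collection schedule.

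**3. When clinic time is known**

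The documents do not say. Outpatients are recruited before the appointment and, if allocated to the videos, are shown them after the baseline surveys, in some cases on a tablet in the waiting room (protocol 3.3 and section 4). Total time in clinic can be complete only after that. SAP 3.6 groups it with videos watched and viewing time, whereas SAP 3.5.3 lists it under baseline values. Number of medications raises no such question: current medications are collected at baseline.

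**4. The stated power**

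Inputs from SAP 1.6: 100 per arm, 15% attrition, 60.0% versus 82.2%, two-sided 5%.

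- Evaluable per arm: 100 × 0.85 = 85. Ratio: 0.822 / 0.60 = 1.37. Difference: 0.222. Mean proportion: 0.711.
- Power = Φ[(0.222 − 1.96 × SE0) / SE1]
- SE0 = √(2 × 0.711 × 0.289 / 85) = 0.0695
- SE1 = √((0.60 × 0.40 + 0.822 × 0.178) / 85) = 0.0674
- Power = Φ[(0.222 − 0.1363) / 0.0674] = Φ(1.27) = 89.8%, against 90% stated

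The figure reproduces as an unadjusted comparison of two proportions. It uses no covariates, so changing the covariate list does not alter it.

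**5. Illustration only**

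Assume that the clinic-time model is fitted to complete cases and that a share of patients, not given in the documents, has no clinic time. The unadjusted formula above then gives:

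| Assumed share without clinic time | Left per arm | Power, 60.0% vs 82.2% |
|---|---|---|
| 10% | 76 | 86.3% |
| 20% | 68 | 82.2% |
| 30% | 59 | 76.5% |
| 40% | 51 | 70.2% |
| 50% | 42 | 61.5% |

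Fractions of a patient are rounded down. An adjusted model would not have exactly these values.

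**The case against.** The best defence is that the dedicated analysis sections largely agree. SAP 3.1 and 5.1.1 give the same four covariates, and 5.1.1 ties its model to table 9. The clinic-time sentence sits in a power section and closely repeats protocol section 7, so it looks like text carried over. That is plausible and points to an easy repair. It does not settle the matter, because no sentence gives one section precedence and the SAP itself contains both models.

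A reader might infer that inpatients will be dropped. The documents do not say so. The restriction to outpatients shows that the authors saw the difficulty, and it could equally mean a separate outpatient model or a term omitted for inpatients. What stands is a missing rule, not a demonstrated loss of patients.

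A reader might also take it as fact that clinic time is measured after randomisation and altered by the videos. The timing is a reasonable inference from the recruitment sequence, but SAP 3.5.3 lists the variable under baseline values. An effect of the videos on visit length is possible and undocumented.

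Finally, the absence of care setting from the models might be read as an error. Randomisation is not described as stratified by setting, so nothing in the design obliges adjustment for it. SAP 3.1 already allows extra adjustment for significant baseline differences. Adding setting here, or to the primary ANCOVA, is a preference.

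**Conclusion.** The contradiction is certain. Satisfaction and adherence have two adjusted models with no covariate in common, no order of precedence, and one place to report the result. The case against clinic time is strong on the missing rule for inpatients and moderate on bias, which rests on inferred timing and an assumed link between the videos and visit length. The conflict with the intention-to-treat rule arises only if the model is fitted to complete cases.

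This should be fixed, but it does not threaten the trial's main result. Only the adjusted secondary analyses are affected. The primary outcome, the sample size and the unadjusted tests and relative risks are unchanged. It would be wrong to conclude that the stated 90% power is lost, because that figure belongs to the unadjusted comparison, which stays in the plan. The lower values in the illustration depend on both an assumed share and complete-case fitting.

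**What to change.** - Delete total time in clinic from the adjusted model in protocol section 7 and SAP 1.6.
- State one adjusted model, that of SAP 3.1, for satisfaction, motivation and adherence: age, gender, education, AF subtype, and the baseline value where collected. Use it identically in SAP 1.6, 3.1 and 5.1.1, which means adding the baseline term to 5.1.1, and have protocol section 7 refer to it.
- Number of medications then leaves the model as well. If the sponsor wants to keep it, it should be the baseline count and appear in every section.
- Say that the adjusted columns of eTable 9 come from this model.
- Report clinic time descriptively only, as SAP 3.6 already provides, and remove it from the baseline listing in SAP 3.5.3 or explain why it belongs there.

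The cost is wording in the protocol and SAP. No new data are needed and no sample size or power figure changes. The edits should be made before outcome data are examined by arm. Adjustment for care setting is optional and not part of this correction.
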